### Primary outcome measures

The primary endpoint in the present study is the ICER analysis (ratio costs / QALY) of these two rTMS therapeutic strategies (arm A or arm B) versus usual chemotherapy, psychotherapy, or ECT without active rTMS (arm C) at 12 months to treat unipolar TRD, according the collective perspective. QALY evaluation is measured by the Euroqol Five Dimension Questionnaire (EQ-5D).

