### Secondary outcome measures

The secondary endpoints in each of the three arms are: ICER at 24 months after the last rTMS or placebo session; the cost–utility ratio analysis over 12 and 24 months; 5-year budget impact analysis of the most efficient therapeutic strategies; and prognosis factors of maintenance after a response to an initial rTMS cure. Moreover, the following criteria will be compared between arms A and C, and between arms B and C: rates of responders; remission; disease-free survival at 12 and 24 months; depressive symptomatology evolution; tolerance; observance; treatment modifications; number of suicide attempts and suicide achieved; marital / professional status; and quality of life at 12 and 24 months.

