### Statistical analysis

Descriptive analysis of the data collected during each patient evaluation will be carried up until the final evaluation. Specific time points for analysis in the three groups are: baseline; at 1 month after the last rTMS or sham sessions; and 12 and 24 months after the end of the first rTMS or sham course. Continuous variables will be described using median, standard deviation, minimal, maximal, and range for quantitative variables; qualitative variables will be described using frequencies and percentages. No data about quality of life, healthcare consumed, and the cost are available in the literature for this indication, making a priori the calculation of number of individuals needed impossible. The number of participants required for the present study was calculated according to the expected and sustained response in each arm (> 50% decrease in MADRS total score). This rate of responder after the rTMS cure is estimated at 60% in arms A and B at 1 year with 50% of success of rTMS [23, 48]. According to the literature, we hypothesized a rate of 30% maintained response at 1 year for arm A [23, 31, 49, 50] and arm B [23, 50–52], and 11% for arm C [53]. Assuming a 5% (bilateral) type I error, a power of 80%, and an attrition rate of 80%, a total of 318 individuals is required (106 in each arm). The study includes three arms, but only two comparisons will be carried out: arm A versus arm C, and arm B versus arm C.

For the ICER, resources consumed, including costs and QALY, will be presented with average and dispersion for each group. The comparison between cost, QALY, and the years of life gained in each arm, including ICER analysis, will be evaluated with the estimation of their standard deviation and their corresponding 95% confidence intervals (CI) following the non-parametric bootstrap method [54]. Tables will present differences between the three groups including their costs, QALY, and ICER. The ICER is calculated to consider the possibilities of vast dominance between these strategies [55]. For example, the ICER between arms A and C will be calculated as follows:

$$ ICER=\frac{C_{armA}-{C}_{armC}}{QALYs_{armA}-{QALYs}_{armC}} $$

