According to health economic criteria, several parameters are necessary to calculate the numbers of individuals in a health economic study including [73]: cost and QALY average deviation over time; costs and QALY standard deviation in each arm; correlation between the costs and QALY difference; and the QALY value. These data are ideally obtained from the literature or a pilot study. However, no source data were available for our study concerning the costs and the quality of life in depression. Moreover, there is no official recommendation available on the QALY monetary value in France [56]. That is why we preferred to calculate the number of individuals required according a clinical criterion, the rate of response at 12 months, rather than a risky health economic hypothesis. This rate of response after the rTMS cure is estimated at 60% in arms A and B, based on the same rTMS protocol already used in French context in that population [48]. According to the literature, we adopted a hypothesis of 30% of sustained response at 1 year in arm A [23, 31, 49, 50] and in arm B [23, 49, 51, 52], and n hypothesis of 11% rate of response sustained at 1 year in arm C [53]. Assuming a 5% (bilateral) type I error, a power of 80%, and an attrition rate of 80%, a total of 318 individuals is required, with 106 in each arm.

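### The SD planned for the primary ICER is not a stable quantity, its CI is unreadable if the QALY gain is small, and the comparison wording must be reconciled with choosing the most efficient strategy

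*Protocol article*

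**What the plan says.** Under Primary outcome measures: "The primary endpoint in the present study is the ICER analysis (ratio costs / QALY) of these two rTMS therapeutic strategies", each against arm C at 12 months. Under Statistical analysis, the quantities to be given an SD and an interval are set out as "The comparison between cost, QALY, and the years of life gained in each arm, including ICER analysis", and these "will be evaluated with the estimation of their standard deviation and their corresponding 95% confidence intervals (CI) following the non-parametric bootstrap method". The ratio itself is therefore to receive an SD and a CI. The only other robustness analysis described for the ICER is a one-way deterministic Tornado analysis of session cost and pricing, which does not address sampling error.

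On which arms are compared, the same section says that "only two comparisons will be carried out: arm A versus arm C, and arm B versus arm C". It also says "Tables will present differences between the three groups including their costs, QALY, and ICER" and "The ICER is calculated to consider the possibilities of vast dominance between these strategies". Secondary outcome measures calls for a "5-year budget impact analysis of the most efficient therapeutic strategies", and Specific aims speaks of one such strategy, in the singular. The Discussion notes that "there is no official recommendation available on the QALY monetary value in France".

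**The concern.** An ICER divides a cost difference by a QALY difference. If the QALY difference may be close to zero, two things go wrong:

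- **The SD.** Resamples with a denominator near zero give enormous ratios of either sign. The computed SD then depends on how close to zero the worst resample happened to fall.
- **The interval.** A negative ICER arises both when rTMS is cheaper and better and when it is dearer and worse. If resamples of both kinds occur, ordering the ratios from low to high does not order them from good to bad, and the limits mix opposite conclusions.

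This is the primary endpoint, so its headline measure of uncertainty may not be interpretable.

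The second issue is one of consistency. A, B and C are mutually exclusive strategies. Which of them is most efficient depends in part on the increment between A and B. One sentence appears to leave that increment out, while other sentences need it or seem to provide it.

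**Working it through.** **No figure to reproduce.** The documents give no SD for cost or QALYs, no expected QALY gain and no precision for the ICER. Only the 106 per arm comes from them. Everything else here is an assumption.

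**Step 1: how often does the QALY difference fall at or below zero?** SE = SD × √(2/n); share = Φ(−gain/SE). For SD 0.25 and n = 106, SE = 0.25 × √(2/106) = 0.0343.

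| Assumed QALY SD, n per arm | SE | Gain 0.02 | Gain 0.05 | Gain 0.10 |
|---|---|---|---|---|
| 0.20, 106 | 0.0275 | 23% | 3.4% | 0.01% |
| 0.25, 106 | 0.0343 | 28% | 7.3% | 0.2% |
| 0.20, 85 | 0.0307 | 26% | 5.2% | 0.06% |
| 0.25, 85 | 0.0383 | 30% | 9.6% | 0.5% |

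The rows with 85 assume that about 80% of 106 are evaluable.

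**Step 2: what happens to the SD and CI?** Non-parametric bootstrap of two arms of 106, QALY SD 0.25, cost SD EUR 10,000, extra cost EUR 2,000. For each gain, one dataset was resampled repeatedly with 1,000 to 100,000 resamples. Percentile limits are assumed, since the article names no type of bootstrap interval. Net benefit = 50,000 × QALY difference − cost difference, where EUR 50,000 is also assumed.

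| Gain | Share ≤ 0 | SD of ICER over runs (EUR) | 95% limits of ICER (EUR, about) | SD of net benefit (EUR) | 95% limits of net benefit (EUR) |
|---|---|---|---|---|---|
| 0.02 | 28% | 0.66 to 23 million | −760,000 to 790,000 | 2,075 | −5,069 to 3,062 |
| 0.05 | 6% | 0.44 to 144 million | −237,000 to 365,000 | 2,112 | −3,615 to 4,672 |
| 0.10 | 0.2% | 21,000 to 1.2 million | −7,000 to 83,000 | 2,281 | −1,484 to 7,489 |

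The SD does not settle in any row, and more resamples do not help. Net benefit is linear in the two differences. Its SD by formula, with cost and QALY uncorrelated, is √[(50,000 × 0.0343)² + (10,000 × √(2/106))²] ≈ EUR 2,200, in line with the bootstrap.

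**Step 3: when can the ratio's limits be read?** At 0.10 almost every resample has a QALY gain, so a negative limit means cost saving. At 0.02 and 0.05 more than 2.5% of resamples have no gain. Large negative ratios then come from small QALY losses at higher cost, a poor outcome that is placed at the apparently favourable end of the scale.

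**Step 4: is a small gain plausible?** The sample size assumes sustained response of 30% against 11%, a difference of 19 points. If the whole gain came from those extra responders, and each kept an assumed utility advantage of 0.2 to 0.4 for the year, it would be 0.19 × 0.2 = 0.04 to 0.19 × 0.4 = 0.08. A gain of 0.10 would need 0.10/0.19 = 0.53 per extra responder. Transient responders could add to the gain, so this shows only that small gains cannot be set aside.

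**Step 5: why A versus B matters.** Invented arm means (QALY; EUR): C (0.60; 15,000), B (0.63; 15,600), A (0.65; 16,600).

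- B v C: 600/0.03 = 20,000 per QALY
- A v C: 1,600/0.05 = 32,000 per QALY
- A v B: 1,000/0.02 = 50,000 per QALY

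Net benefit at EUR 40,000 per QALY: C 24,000 − 15,000 = 9,000; B 25,200 − 15,600 = 9,600; A 26,000 − 16,600 = 9,400. B is best. At 60,000: C 21,000; B 22,200; A 22,400. A is best. The choice turns at 50,000, which is the A-versus-B increment and neither of the ratios against C.

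**The case against.** Several objections have force.

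- **The uncertainty is not lost.** Bootstrap CIs are also planned for the cost and QALY differences, and they remain valid. A reader might infer that the whole primary analysis is unusable. The documents do not support that.
- **The CI problem is conditional.** At a gain of 0.10 the ratio's interval was readable, and the documents neither state nor exclude such a gain. The article does not specify percentile limits, and the cited bootstrap source is not at hand. This limits the point about the interval. It does not rescue the SD, which was unstable at 0.10 as well.
- **An article may leave net benefit, the plane and acceptability curves to the analysis plan.** This is accepted, and their absence is not the fault. The fault is the SD and CI of the ratio that the article does specify.
- **A versus B is not shut out.** A reader might infer that the plan compares only against C and so cannot identify the most efficient strategy. But it promises cost and QALY means for each group, three-group tables of differences and attention to dominance between strategies. The A-versus-B increment follows from the arm means. The restrictive sentence closes the sample-size paragraph, and later paragraphs compare A with B on relapse-free survival and rating scales.
- **No wrong choice is shown.** The plan states no rule for choosing the strategy. In the example at EUR 40,000, ranking by the ratios against C picks B, which is the right arm. One cannot say that the plan would choose wrongly.

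What remains of the second issue is a conflict of wording and an unstated role for the A-versus-B increment.

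**Conclusion.** The point holds in a limited form. The article attaches an SD to the primary ICER, and that SD was unstable under every gain examined. The accompanying CI cannot be read if the true gain is about 0.02 to 0.05 QALY, where some 3% to 30% of resampled QALY differences fall at or below zero over the assumed SDs and sample sizes. It is largely unaffected at 0.10. These sizes rest on assumed SDs, costs, gains and percentile limits, because the documents supply none of them. The conclusion about the SD depends much less on those values, since it follows from dividing by a quantity that can come near zero.

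On the arms, the documents are inconsistent: a sentence allowing two comparisons stands beside three-group tables and a budget impact that needs a most efficient strategy. This calls for reconciliation and does not show that the arms cannot be ranked.

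**What to change.** 1. Delete the SD of the ICER. Report the ICER as a point estimate with the cost-effectiveness plane, and keep the planned bootstrap CIs for the cost and QALY differences.
2. Base inference on incremental net monetary benefit with bootstrap CIs, and on an acceptability curve containing all three arms, over a stated range of QALY values. This displays results without needing an official French value; it does not supply one.
3. State that the two powered comparisons are A versus C and B versus C, that the A-versus-B increment is reported as an unpowered estimate, and that the strategy for the budget impact is chosen from the full incremental or net-benefit ranking of the three arms.

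The cost is a change of analysis wording and a little programming on the same bootstrap samples, with no new data or patients. The downside is that results appear over a range of QALY values rather than as one interval, and the preferred arm may change within that range.

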*C*_*armA*_ and *C*_*armC*_ correspond to the costs of depression in each arm and are the QALYs’ gain associated with the rTMS maintenance versus usual cares without rTMS (placebo). At the end, a univariate and determinate sensibility analysis will be estimate with the Tornado method to evaluate the robustness of the resultants concerning the variation in the cost of rTMS sessions and the hypothesis of their pricing.

To estimate the costs of depression, clinical data matching the eCRF and the NHSD will be applied using the patient identification number. If there is a baseline deviation between arms of the study about the quality of life estimated with the EQ-5D, two analyses will be conducted: one with the quality of life raw score; and another with adjusted scores using a logistic regression model [56]. The cost–utility and EQ-5D analysis will be conducted according to the intent-to-treat (ITT) principle on two samples: one sample with completed cases including participants with completed data; and another with an imputed sample in which missing data about cost and quality of life will be imputed according a multiple imputation method.

The rate of remission with their corresponding 95% CIs at 12 and 24 months will be compared between arm A versus arm C, and arm B versus arm C according to the generalized linear model (logistic model) to consider the repeated measurements as a random factor (stratification factor of the randomization). Plots of relapse-free survival at 12 and 24 months will be estimated according to the Kaplan–Meier method; they will be compared between arms A and B, and between arms B and C using the Log-Rank stratified test in each center. A Cox multivariate analysis will be applied to evaluate the sustainability of the response in the time.

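### QALYs are adjusted for baseline EQ-5D only after an undefined imbalance, and by a logistic model that cannot give the mean QALY difference the ICER needs

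*Protocol article*

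**What the plan says.** Under Primary outcome measures, the primary endpoint of the protocol article is the 12-month ICER of arm A or arm B against arm C, with QALYs derived from the EQ-5D. The formula under Statistical analysis puts the difference in QALYs between two arms in the denominator. The same section describes costs and QALYs as arm averages with "corresponding 95% confidence intervals (CI) following the non-parametric bootstrap method". It mentions no covariates there.

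Baseline adjustment appears once, and it is conditional: "If there is a baseline deviation between arms of the study about the quality of life estimated with the EQ-5D, two analyses will be conducted". The two are "one with the quality of life raw score; and another with adjusted scores using a logistic regression model". The article states no test or threshold for a deviation and does not say which of the two results feeds the ICER. The next sentence plans both a complete-case sample and a multiply imputed sample.

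**The concern.** Two things are wrong in the text itself.

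- **The model does not fit the quantity.** An EQ-5D utility and a 12-month QALY are continuous. The ICER needs a difference in means, and a logistic model does not return one.
- **The trigger is undefined and comes after the data.** Baseline utility is a likely predictor of the QALY that follows. Adjusting for it only after an imbalance has been noticed gives up precision in all other cases. When an imbalance is noticed, two results stand side by side with no stated order.

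At stake is the denominator of the primary endpoint, in a trial whose size was set on clinical response and not on costs or QALYs.

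**Working it through.** The article gives no figure for QALY precision, so there is none to reproduce. I take 106 per arm as printed. Whether that number follows from its own inputs is a separate question and does not affect this point.

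**Inputs**
- n = 106 per arm (Statistical analysis).
- Baseline EQ-5D is not balanced by design: permuted blocks by centre, with no stratification or minimisation (Randomization).
- Correlation ρ between baseline EQ-5D and 12-month QALY: not given. The article states "No data about quality of life, healthcare consumed, and the cost are available in the literature for this indication". Assumed 0.3, 0.5 and 0.7.
- Trigger: not given. Assumed to be a baseline test with p < 0.05.

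**Step 1: the model.** The ICER formula needs mean QALY in arm A (or B) minus mean QALY in arm C. Logistic regression of a binary outcome gives a log odds ratio. No binary EQ-5D outcome is defined, and no step back to a mean is described. No other part of the article supplies a continuous-outcome adjustment for EQ-5D or QALYs. The same section also names a mixed logistic model for the MADRS, MARS, CRS and CGI scores, so the mismatch is not confined to one sentence.

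**Step 2: precision from always adjusting.** For a linear model on baseline:
- SE(adjusted) / SE(raw) = √(1 − ρ²)
- equivalent n = 106 / (1 − ρ²)
- power of a contrast that has 80% unadjusted = Φ[(1.960 + 0.842)/√(1 − ρ²) − 1.960]

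| ρ | SE ratio | Equivalent n per arm | Power |
|---|---|---|---|
| 0.3 | √0.91 = 0.95 | 106/0.91 = 116 | 84% |
| 0.5 | √0.75 = 0.87 | 106/0.75 = 141 | 90% |
| 0.7 | √0.51 = 0.71 | 106/0.51 = 208 | 98% |

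**Step 3: how much the conditional rule recovers.** This used 20,000 simulated trials under no effect, with 106 per arm and outcomes in SD units. The check is generous to the plan, because it uses a linear adjustment when the trigger fires. It also lets the adjusted result replace the raw one, whereas the plan reports both.

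| ρ | SD of estimate: raw | Adjust only if p < 0.05 | Always adjust | Type I error of conditional rule |
|---|---|---|---|---|
| 0.3 | 0.137 | 0.136 | 0.131 | 4.8% |
| 0.5 | 0.137 | 0.132 | 0.119 | 4.2% |
| 0.7 | 0.138 | 0.129 | 0.099 | 3.7% |

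The raw SD agrees with √(2/106) = 0.137. At ρ = 0.5 the conditional rule recovers (0.1367 − 0.1319)/(0.1367 − 0.1188) = 0.0048/0.0179, about 27% of the available reduction in SD. With 85 per arm the pattern is the same (0.154, 0.148 and 0.133 at ρ = 0.5).

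**Step 4: trials in which an imbalance occurs.** Among trials with baseline p < 0.05, the raw difference is shifted towards the favoured arm by 0.099, 0.165 or 0.220 SD at ρ = 0.3, 0.5 or 0.7. As a check, the mean of |Z| given |Z| > 1.96 is 0.0584/0.025 = 2.34, and 2.34 × 0.137 × ρ gives 0.096, 0.160 and 0.224. In those trials the raw test rejects a true null in 10%, 18% or 32%.

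**The case against.** The strongest reply is that the analysis feeding the ICER is sound. The adjusted analysis is added to the raw one, not substituted for it. The raw difference with its bootstrap interval is therefore produced in every case, and it is unbiased over all randomisations. That stands. It rules out the inference that the primary result is biased or that its error rate is inflated: with the assumed trigger, the conditional rule stays below 5%. Only if a deviation were always declared, and the more favourable of the two results then chosen, would the rate exceed 5% (6.5%, 7.2% and 8.4% at the three correlations). The article describes no such choice.

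A second reply is that the logistic wording may be a slip in a condensed article, or shorthand for a fractional-logit or propensity method explained in the reference attached to that sentence. This is possible, and the text does not show that utilities will be dichotomised. But it describes neither method, so the statement as printed still needs correction.

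A third reply is that the sizes rest on assumptions. That also stands. A reader might infer that a chance baseline difference passes straight into the QALY and rivals the treatment effect. Only a fraction set by the slope passes through, and the article gives no expected QALY gain for comparison.

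A reader might also object that raw or adjusted, crossed with complete-case or imputed, leaves several ICERs with no base case, and that complete cases are placed under intention to treat. Multiple imputation is already planned, and naming the base case is commonly left to an analysis plan, which is not at hand. I do not press that as an error.

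**Conclusion.** The point holds in a limited form. Two defects are plain in the text and need no assumed number: a logistic model named for a continuous score, and an adjustment that depends on an undefined deviation. The consequences are:

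- an adjusted analysis that cannot be used as written;
- lost precision when no deviation is declared;
- conditional bias of the raw result when an imbalance does occur;
- two results with no ranking between them.

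The validity of the unadjusted comparison over repeated randomisation is not in question. The precision at stake depends wholly on the assumed correlation: slight at 0.3 (SE about 5% lower) and large at 0.7 (about 29% lower). The conditional figures further assume a p < 0.05 trigger.

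**What to change.** Delete the imbalance trigger and the logistic model. State that the 12-month QALY difference for each comparison will always be estimated by linear regression of QALY on arm, baseline EQ-5D utility and centre. Refit the model within each bootstrap resample, so that the adjusted difference feeds both the ICER and its interval. Apply it to the multiply imputed sample of all randomised patients, and report the unadjusted and complete-case results as sensitivity analyses.

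The cost is a change of wording in the protocol or analysis plan, plus modest programming. Baseline EQ-5D is already needed for the comparison the article plans, and centre is known from randomisation, so no new data are required.

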## Methods/design

### Study design, setting, and recruitment

This is a health-economic, prospective, randomized, double-blind, multicenter, parallel-arm study funded by the French Ministry of Health (Reference: 030/2018). The sponsor is the Centre Hospitalier Universitaire (University Hospital) of Nantes, France. The patients are randomly assigned to (Fig. 1):
▪ Arm A with active rTMS cure and systematic maintenance M-rTMS for responders (> 50% decrease in MADRS total score);▪ Arm B with a new course of active rTMS at the first sign of depression relapse or recurrence for responders;▪ Arm C with sham cure. In this arm, 50% of responders have systematic placebo rTMS maintenance after the cure (arm C1) and the other 50% have placebo rTMS cure at the first sign of depressive relapse or recurrence (arm C2).

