### Randomization

During the baseline inclusion visit, the inclusion and exclusion criteria are checked and participants randomized by center into three groups by a computerized random number generator with a permuted block design without stratification or minimization. Participants are randomized to one of the treatment arm using a computer program included in the electronic case report form (eCRF). Initial randomization is performed according the ratio 1:1:0.5:0.5, respectively, corresponding to arm A, arm B, arm C1 (systemic sham rTMS maintenance for responders), and arm C2 (sham rTMS maintenance at the first sign of depressive relapse or recurrence for responders). Block size and type of variation (fixed or randomly) are not known by the investigators to maintain adequate blinding. Randomization occurs in a recorded delay of maximum 15 days before first rTMS or placebo session.

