### Follow-up

Investigators will meet volunteer participants 2, 6, 9, 12, 18, and 24 months after the last rTMS session (Fig. 2). A patient who fails to respond to therapy (no decrease of > 50% in the MADRS score) despite 6 weeks of treatment will continue longitudinal follow-up to avoid selection bias. A telephone call is realized at 15 and 21 months outside the follow-up consultations to keep in contact with the participants and evaluate the EQ-5D, the patient questionnaire including the Word Productivity and Activity Impairment (WPAI) and formal / informal cares consumption, rTMS side effects, and treatment modifications. The study will last 4 years in total (2018–2022) with 24 months dedicated to the enrollment period and 24 months for longitudinal follow-up (Fig. 1).

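### Relapse-free survival is tested against sham without a stated risk set; on its natural reading, arm C comparisons use responder groups formed after randomisation by the treatment itself

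*Protocol article*

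**What the plan says.** In the protocol article, Statistical analysis, the endpoint and estimator are fixed: "Plots of relapse-free survival at 12 and 24 months will be estimated" by Kaplan–Meier. For the test, "they will be compared between arms A and B, and between arms B and C using the Log-Rank stratified test in each center". A model follows: "A Cox multivariate analysis will be applied to evaluate the sustainability of the response in the time". Secondary outcome measures lists disease-free survival at 12 and 24 months among the criteria compared between A and C and between B and C. So the sham arm enters as B v C in one section and as both A v C and B v C in the other.

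No risk set, time origin or rule for non-responders is given for this endpoint. Intention to treat is stated only for the cost–utility and EQ-5D analysis.

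Three other statements bear on who can relapse:
- Study design, setting, and recruitment: "Arm B with a new course of active rTMS at the first sign of depression relapse or recurrence for responders".
- Randomization: "Randomization occurs in a recorded delay of maximum 15 days before first rTMS or placebo session". Response is therefore known only after allocation and after an active or sham course.
- Follow-up: patients who do not respond "will continue longitudinal follow-up to avoid selection bias".

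**The concern.** Inclusion requires a MADRS score of at least 20, so nobody is free of the episode at randomisation, and relapse becomes possible only after response. For a comparison with arm C, two ways of filling the risk set suggest themselves, and neither estimates the effect of the assigned strategy.

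- **Responders only.** Active responders are compared with a probably smaller group of sham responders. The treatment under test decides who enters, so randomisation no longer protects the contrast.
- **Everyone, with non-responders never having an event.** The arm with fewer responders has fewer patients who can relapse and looks better for that reason.

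Disease-free survival is a named secondary comparison and would be read as evidence of lasting benefit. Either reading could give a null or reversed result while the trial's own hypothesis is true.

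**Working it through.** **Inputs from Statistical analysis.** Initial response in arms A and B is 60%, of which 50% is kept, giving 30% maintained at 1 year. Maintained response in arm C is 11%. There are 106 patients per arm.

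**Not given.** The initial response to sham, *s*, is an assumption and is shown from 15% to 40%. The Discussion calls rTMS twice as effective as placebo; half of 60% would put *s* near 30%.

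**1. The plan's own figure.** The two-proportion formula with pooled variance, 30% v 11%, 80% power, gives 70 per arm at two-sided 5% and 85 per arm at two-sided 2.5%. With 20% attrition, 85/0.8 = 106.25, which reproduces 106. This needs the 5% split over two comparisons and the printed 80% attrition read as 80% retained, which is a separate matter. What counts here is that the trial was sized on 30% v 11% of **all randomised** patients.

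**2. Responders only, B v C.**
- Kept at 1 year among responders: B, 0.30/0.60 = 50%; C, 0.11/*s*.
- With exponential relapse, HR (B relative to C) = ln(0.50)/ln(0.11/*s*).
- Responders: B, 106 × 0.60 = 63.6; C, 106 × *s*.
- Events by 12 months: D = 63.6 × 0.50 + 106*s* × (1 − 0.11/*s*).
- Power = Φ(|ln HR| × √[D·p(1 − p)] − 1.96), where p is B's share of responders.

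Example, *s* = 30%: C keeps 0.11/0.30 = 36.7%. HR = 0.693/1.003 = 0.69. D = 31.8 + 20.1 = 51.9. p = 63.6/95.4 = 0.667. Power = Φ(0.370 × 3.40 − 1.96) = Φ(−0.70) = 24%.

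| Assumed *s* | C responders | C keeps | HR, B v C | Chance of a significant result |
|---|---|---|---|---|
| 15% | 15.9 | 73% | 2.24 | 33% simulated, all but a trace favouring sham |
| 20% | 21.2 | 55% | 1.16 | 6% |
| 22% | 23.3 | 50% | 1.00 | 5.9% simulated (the test's own error rate) |
| 25% | 26.5 | 44% | 0.84 | 8%, favouring active |
| 30% | 31.8 | 37% | 0.69 | 24% (27% simulated), favouring active |
| 40% | 42.4 | 27.5% | 0.54 | 67% (69% simulated), favouring active |

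The simulations used 1,500 trials per row, unstratified, without attrition. With 85 per arm, power is 20% at *s* = 30% and 58% at *s* = 40%. The plan's 30% and 11% hold in every row. A v C gives the same table, because arms A and B carry the same assumptions.

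**3. Everyone at risk, non-responders without events.** Relapse by 12 months is 0.60 × 0.50 = 30% in B and *s* − 11% in C. Arm C looks better whenever *s* − 11% < 30%, that is, for *s* below 41%. At *s* = 22% the contrast is 30% v 11% in sham's favour, and at *s* = 30% it is 30% v 19%. In simulation (1,000 trials per case) the log-rank test significantly favoured sham in about 94% and 44% of trials.

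**4. All randomised, non-responders failing at time zero.** With 106 per arm, simulated log-rank power is 97% to 99.6% for *s* from 15% to 40%. Comparing 30% with 11% directly as proportions has 93% power.

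**The case against.** Much of the case on the other side stands.

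- **The population is not written down.** Responders-only follows from the meaning of relapse and from the arm descriptions, not from an explicit sentence. A condensed article may leave the risk set to the full protocol or SAP. A third reading, with non-responders failing at time zero, is open because Secondary outcome measures calls the endpoint disease-free survival. A reader might infer that the analysis can only be done in responders, or that non-responders are certainly dropped. The document supports neither.
- **A v B is not affected.** Both arms receive the same active first course and differ only in what responders receive afterwards. Becoming a responder therefore does not depend on the contrast, and a responder-only A v B comparison is reasonable.
- **The Cox model has a proper use.** Prognostic factors for maintenance after response are a stated secondary endpoint that is conditional on response by design.
- **The exact null is an assumption.** HR = 1 needs a sham response of 22%, at which sham responders keep their response as often as active ones. At 40% the test has moderate power.
- **The strategy is also compared in other ways.** Response and remission rates are compared with arm C, and the primary endpoint is the ICER.

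What remains: the article has chosen an endpoint and a between-arm test, and the two most direct readings fail against arm C. The reading that works is a different endpoint, sustained response, and the article does not state it.

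**Conclusion.** The concern holds for the comparisons with arm C: B v C in Statistical analysis, and A v C as named in Secondary outcome measures. It does not extend to A v B among responders or to a prognostic Cox model.

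On the responder-only reading, the hazard ratio runs from about 2.2 against active treatment to 0.54 in its favour as the assumed sham response moves from 15% to 40%, with power of about 25% at 30%. It would be too strong to say that the test will show no difference; it can, depending on a rate the plan does not give. The loss of the randomised comparison does not depend on that rate.

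The sizes rest on exponential relapse, on the 11% representing initial sham response that was kept, and on arm B's 30% counting no one who relapsed and responded again. If it does include such patients, time to first relapse in arm B is shorter than assumed here. The point is worth correcting because the endpoint is a named secondary one and the remedy is wording.

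**What to change.** For the comparisons with arm C, define the endpoint in all randomised patients as time in sustained response from the end of the first course, with patients not in response at that point counted as failures at time zero. Test it with the centre-stratified log-rank test already planned. Alternatively, compare the proportion in sustained response at 12 and 24 months, which is the quantity the trial was sized on. State whether a relapse followed by a new response ends sustained response, with one rule for all arms, and judge relapse at the visits common to all arms.

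Show responder-only curves against arm C as descriptive, without a test. Keep the responder-only A v B comparison and the Cox model for prognostic factors, and label both as conditional on response.

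Cost: wording only, because non-responders are already followed. Downside: many events fall at time zero, so the curve mixes initial response with durability; the descriptive responder curves separate the two.
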